**3.5. Interventions**

After randomization, clinical specimens from TB suspects will be submitted to MGIT or culture in Löwenstein Jensen solid medium (gold standard) at the HUCCF-UFRJ Mycobacteriological Laboratory. The accomplishment of such tests does not incur in risk for the patient.

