**3.5.1. Description of the tests**

Respiratory and non-respiratory specimens, naturally contaminated, will be collected in disposable receptacle. The specimens should be given to the laboratory up to 24 hours after being collected and will be submitted to bacilloscopy after the Ziehl-Neelsen coloration. After being processed by the Kubica method, they will be cultivated by the BACTEC MGIT 960 method and in Löwenstein-Jensen in Rio de Janeiro and in Vitoria, and by the BACTEC MGIT 960 method. Cultures contaminated by other microorganisms will be called as contaminated and considered as negative for calculation in statistical tests. In the clinical specimens of the included patients, the sensitivity test will be carried out by the gold pattern tests and by BACTEC MGIT 960. Additionally, the positive cultures will be appraised as for the sensitivity of *M. tuberculosis* for isoniazid, rifampicin, streptomycin and ethambutol by the indirect test of proportions (one strain/patient).

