**3.6. Randomization - Clinical procedures for Open Clinical Trial Practice**

The physician that routinely evaluates the patients under active TB suspicion, invited to voluntarily participate of the study, once deciding the patient's inclusion in the protocol will request an envelope that contains in its external side four key questions: a) which is the patient's probability to present TB (high/intermediary or low); b) the choice above was based in the results of radiological examination; c) in his/her opinion, should the patient begin anti-TB treatment (yes or not) d) what is the patient's risk of having resistant TB (high/intermediary or low). The four questions filled out, the doctor will open the envelope and inside it he/she will identify which is the diagnostic method that should be requested for the patient. The envelopes will be numbered in growing order and the indication of the diagnostic tests inside them has been previously randomized by a professional non-participant of the study. This procedure **attempts to guarantee the concealing of the randomization and at the same time it will be possible to check the success of the randomization**.

In the routine investigation of patients under TB suspicion, the following information is collected in standardized forms: a) socio-demographic data; b) organs and human body systems examination; c) exposure to TB, disease and treatment history; d) past pathological history; e) physical exam; f) chest X-ray result; g) tuberculin skin test result; h) HIV test result.

Respiratory specimens include spontaneous sputum, induced sputum and bronchoalveolar wash. Non-respiratory specimens include biopsy material and synovial, pleural, CSF liquids, etc. A minimum of two and a maximum of three specimens per patient will be appraised in this study. Clinical specimens will not be collected out of the TB diagnostic investigation routine in the hospital.

Following the routine, the clinical samples will be forwarded to the mycobacteriology laboratories in the next working day. Only in the clinical samples of patients that have received randomization for the MGIT, should the laboratory personnel be informed that the MGIT must be performed.

To analyze the outcome of the study, the key information below, present in the medical handbooks or routine record cards of the TB Program, will be copied to the study’s own forms.

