The identification number (ID), the collection date, the specimen volume and the position in the freezer will be registered on the requisition forms of the laboratory and introduced into the computer for all the deposited specimens. The computer files of these forms will be used to create specimen lists for each box of specimens. Two years after the conclusion of the study, the identifiers, excluding the ID number of the study, will be suppressed from the computerized data files and from the paper files.

**3.7. The patient's evaluation during the diagnostic investigation phase (total of 8 weeks) and anti-TB treatment (total of 24 weeks)**

All the patients will be clinically evaluated and continually monitored during the first 8 weeks of the diagnostic investigation phase. Those who receive an active TB diagnosis will be monthly monitored until the end of the drug treatment. The information below, collected in the routine follow-up of the Hospital Tuberculosis Program, will be obtained in the weeks 2, 4, 8, and 24 will be registered in the forms of the study:

▪ Weight

▪ Signs and symptoms associated with TB (e.g. cough, fever, sweating, weight loss, haemoptysis)

▪ Signs and symptoms associated with adverse effects of the drugs of the study (e.g. cutaneous rash, dizziness, fatigue, weakness, anorexia, nauseas, vomiting, diarrhea, abdominal flabbiness, jaundice, neuropathy, palpitations)

▪ If a patient develops new signs or of worsening and symptoms of pulmonary TB, a new chest teleradiography will be performed and three sputum specimens shall be obtained for TB culture and sensitivity tests. If a patient develops signs and symptoms of extra-pulmonary TB, cultures from the appropriate places of the body will be obtained.

Monthly evaluations in the weeks 4 and 24 will include the above indicated procedures and:

▪ A complete hemogram (blood count) with platelet count, creatinine, ALT, AST, Gamma GT, total bilirubin and fractions and alkaline phosphatase

▪ Sputum specimens (2) for direct bacilloscopy (Baar research) and culture for mycobacterium

▪ If a patient is unable of producing sputum naturally, the sputum shall be induced by hypertonic saline solution inhalation

▪ A chest radiography performed in week 8

▪ Drugs sensitivity test accomplished in weeks 8 and 24

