**3.8. Definition of a TB Suspect Case, Active TB Case and Discordance Analysis**

**Pulmonary and /or pleural pulmonary form**

Every patient under pulmonary TB suspicion that presents respiratory signs/symptoms and with alterations in the chest X-ray will be classified in three groups;

a) Typical pattern of TB: infiltrated in upper third (LS or apical seg of LI), with or without cavity; bilateral miliar infiltration; unilateral pleural hemorrhage with upper lobe infiltration .

b) Intermediate pattern of TB: infiltrated in middle or lower third, with or without cavity in these areas; isolated pleural hemorrhage, infiltrated in upper thirds of undetermined activity; diffuse abnormalities (not miliar); mediastinal or hilar enlargement .

c) Atypical Pattern of active TB: multifocal hypotransparency images; alveolar hypotransparency images; calcified nodules.

“**Confirmed TB case"** will be defined as the patient with at least one positive culture for *M. tuberculosis* in L-J or MGIT960*.*

**“Probable TB case"** will be defined as the patient that presents negative results to culture with one or more of the following characteristics:

a) clinical answer to the treatment (defined as improvement to X-ray, b) decrease of the cough and 3% weight gain in relation to the beginning of the treatment) and absence of alternative diagnosis;

Patient not classified as confirmed case or probable TB will be considered "non- TB."

**Treatment failure:** patient that remains with positive bacteriological test (two samples in a 30 day interval) after 5 months of treatment, standardized by MH

High risk factors for resistant TB:

a) Relapsing TB (previous complete treatment for TB with apparent cure), b) Treatment failure (patient under treatment ≥ 4 months with positive bacilloscopy), c) Patient’s contact with multidrug resistant-TB.

3.9 **Main outcome**  The primary outcome was defined as the proportion of patients in each group whose initial prescription changed by the second month after randomization. The ‘change’ could be initiating or stopping TB treatment.

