**Secondary outcomes-**

-The secondary outcomes were the mean time to changing the initial clinical prescription,

-The proportion of patients with positive culture and positive smear microscopy for TB,

-The proportion of patients initiating treatment before test results,

-The occurrence of severe adverse events

-Patient satisfaction with the overall treatment- Number of deaths by any cause in the patients included in the study.

- Proportion of patients with TB diagnosis sensitive or resistant to anti-TB medicines (RIF, INH, SM and EMB), with the methods employed in the study.

- Proportion of patients that undergo anti-TB treatment failure during the therapy.

- Proportion of drug resistant TB development in the patients that used the different diagnostic methods and that were classified as treatment failures.

- Proportion of bacteriological conversion (bacilloscopy and culture for mycobacterium) due to the anti-TB treatment at the end of the second and sixth month of anti-TB treatment.

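### The protocol does not say which culture medium judges conversion and treatment failure, and its one arm-specific laboratory rule, taken literally, lets the tests under comparison measure these outcomes

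*Protocol*

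**What the plan says.** **Media by arm.** Three statements do not agree.

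- Section 3.5 makes the media alternatives after randomisation: "clinical specimens from TB suspects will be submitted to MGIT or culture in Löwenstein Jensen solid medium (gold standard").
- Section 3.5.1 describes both media, with no split by arm: "they will be cultivated by the BACTEC MGIT 960 method and in Löwenstein-Jensen in Rio de Janeiro and in Vitoria". It also counts contaminated cultures as negative.
- Section 3.6 (Randomization) gives the laboratory rule: "Only in the clinical samples of patients that have received randomization for the MGIT" is the laboratory told to run MGIT. The rule is tied to the patient's allocation and mentions neither visit nor type of specimen.

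**Follow-up cultures.** Section 3.7 asks for "Sputum specimens (2) for direct bacilloscopy (Baar research) and culture for mycobacterium" and names no medium. It places these under the evaluations at weeks 4 and 24. Week-8 specimen collection appears in the list of study forms.

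**Outcomes.** The secondary outcomes include "Proportion of bacteriological conversion (bacilloscopy and culture for mycobacterium") at the end of the second and sixth months, and the proportion with treatment failure. Section 3.8 defines failure by a "positive bacteriological test (two samples in a 30 day interval) after 5 months of treatment", again with no medium. Section 3.11 summarises dichotomous outcomes by group, with relative risk, risk difference and number needed to treat.

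**The concern.** The arms differ in the culture system used. If the same system also reads the follow-up sputum, two patients with the same response to treatment can be classified differently only because of their allocation. A medium that recovers more residual organisms shows fewer conversions and more culture-based failures. A medium that loses more cultures to contamination shows the opposite, because contaminated cultures count as negative. Neither is an effect on patients, yet the planned risk difference would present it as one.

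This cannot be repaired at analysis. If LJ was never inoculated for follow-up samples in the MGIT arm, no common measurement exists to return to.

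**Working it through.** **Step 1: what each reading of the text implies for follow-up cultures.**

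| Reading | MGIT arm | LJ arm | Same measurement? |
|---|---|---|---|
| 3.5 and 3.6 apply at every visit | MGIT | LJ | No |
| 3.5.1 as LJ for all, with MGIT added under the 3.6 rule | LJ + MGIT | LJ | No, one arm has an extra chance of a positive |
| 3.5.1 as both media for everyone | LJ + MGIT | LJ + MGIT | Yes, but contradicts 3.5 and 3.6 |
| Allocation covers diagnostic specimens only; follow-up by programme routine | LJ | LJ | Yes, but stated nowhere |

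The two readings that give a common measurement need either a contradiction of the randomised comparison or an assumption that the protocol does not write down.

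**Step 2: size of the artefact.** The protocol gives no figure for these outcomes. Its sample size of 770 concerns the primary outcome and does not enter here.

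Inputs:
- t, the proportion truly culture-positive at month 2, equal in both arms: assumed 20% to 30%.
- LJ sensitivity: assumed 80%, the lower end of the 80–85% that the Rationale gives for culture in diagnosis.
- MGIT sensitivity: assumed 80% to 95%. The Synopsis calls MGIT results similar to those on solid medium and gives no figure, so equality is included.

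Apparent conversion = 1 − t × s. Spurious difference = t × (s_MGIT − s_LJ).

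| t | LJ (80%) | MGIT 80% | MGIT 85% | MGIT 90% | MGIT 95% | Difference (points) |
|---|---|---|---|---|---|---|
| 20% | 84.0% | 84.0% | 83.0% | 82.0% | 81.0% | 0 to 3.0 |
| 30% | 76.0% | 76.0% | 74.5% | 73.0% | 71.5% | 0 to 4.5 |

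Largest case: 0.30 × (0.95 − 0.80) = 0.045. With LJ at 85%, it is 0.30 × (0.95 − 0.85) = 0.030.

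**Step 3: both media in one arm.** Equal accuracy does not by itself remove the artefact here. With 80% for each medium, the sensitivity of either being positive lies between 80% (fully dependent) and 1 − 0.20 × 0.20 = 96% (independent). At t = 30% the difference is 0 to 0.30 × 0.16 = 4.8 points.

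**Step 4: contamination.** If a share c of cultures is contaminated and counted as negative, apparent conversion becomes 1 − t × s × (1 − c). A higher c raises apparent conversion. The protocol gives no contamination rates, so only the direction can be stated.

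**Step 5: denominator.** A conversion needs a positive result at baseline. Baseline culture positivity is itself set by the allocated medium, so a common follow-up medium alone would still leave differently selected groups.

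**The case against.** A reader might infer that the protocol prescribes a different follow-up medium in each arm. It does not; no sentence names the follow-up medium. The text around the laboratory rule points towards diagnostic samples. The envelope names a diagnostic method, "A minimum of two and a maximum of three specimens per patient will be appraised in this study", and specimens are to come only from the routine diagnostic work-up. Section 3.5 speaks of TB suspects, not of patients on treatment. Section 3.7 draws follow-up information from the TB programme's routine, and section 3.5.1 mentions both media. A common LJ culture at follow-up is therefore a fair reading, and this part of the objection stands. It does not close the gap, because that reading is never stated. Section 3.7 also asks for two further sputum specimens at follow-up, so the limit of two to three either covers diagnostic specimens only or conflicts with that section.

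Smear is the same in both arms. It forms part of conversion and can by itself satisfy the failure definition. That stands too, and no size is given here for failure.

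The magnitudes are assumed, and equal accuracy gives zero when each arm uses one medium. Larger gaps could be produced by assuming that LJ performs much worse at low bacterial load, but the protocol offers nothing to support such values.

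**Conclusion.** The point holds as an unresolved conflict, not as a stated design choice. Sections 3.5, 3.5.1 and 3.6 disagree on which media are used in which arm, and the follow-up and outcome sections name none. Under the literal laboratory rule, culture conversion at months 2 and 6 and culture-based failure would be measured partly by the tests being compared.

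Under the stated assumptions the spurious difference in month-2 culture conversion is 0 to 4.5 points with one medium per arm, and up to 4.8 points if MGIT is added to LJ in one arm only. A difference in contamination could offset or reverse it. The effect is smaller where smear decides the outcome. Only secondary outcomes are touched; the primary outcome, change of prescription by the second month, is not measured by follow-up culture.

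**What to change.** 1. Reconcile sections 3.5, 3.5.1 and 3.6, stating which media are inoculated in each arm, for which specimens and at which visits. Align the follow-up culture weeks in section 3.7 with the list of study forms and the month-2 outcome.
2. State that, for the between-arm comparison, conversion and failure are judged in both arms on the same methods: smear and the routine LJ culture. Any MGIT follow-up result is left out of that comparison but is not barred from clinical use.
3. Fix a denominator that does not depend on the allocated medium, for example patients smear-positive at baseline, or all randomised patients. With all randomised patients, count those still positive on the common methods, since a count of conversions would again need a baseline culture result.

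The cost is a few sentences, plus LJ inoculation of follow-up samples in the MGIT arm. Section 3.5.1 describes LJ inoculation as part of the laboratory's daily work, so the added burden is small.

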**3.10. Size Sample**

Concerning the primary outcome, the smallest absolute difference considered important by a panel of specialists working at HUCFF was 10% presents the number of patients required to have an 80% chance of detecting this difference at the 5% level of statistical significance. We intended to recruit at least 770 participants.

**3.11 -. Data analysis**

Socio-demographic and clinical characteristics between groups at trial entry will compared. For dichotomous outcomes, we will calculate the proportions for both groups, and for continuous outcomes, we will calculate the means, standard deviations and medians. We will used intention-to-treat analysis to calculate the relative risk, the risk difference, the number needed to treat and the 95% confidence intervals for these parameters. No subgroup analysis will be pre-specified. All analyses will be performed using SPSS software

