**3.1 - Location of the Study**

1. Hospital Complex: Clementino Fraga Filho University Hospital and Chest Diseases Institute of the Federal University of Rio de Janeiro (HUCFF-IDT/UFRJ), located in the city of Rio de Janeiro.

2. Policlínica Augusto Amaral Peixoto (PAAP) – Municipality Health Secretary - Rio de Janeiro, Brazil.

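### Section 3.11 names no covariate adjustment for the primary comparison, although two relevant envelope answers are written before allocation is revealed; adjusting for them would add precision at almost no cost

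*Protocol*

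**What the plan says.** The primary outcome (Protocol 3.9) is the "proportion of patients in each group whose initial prescription changed by the second month after randomization", where a change may be starting or stopping TB treatment. For the comparison, section 3.11 states: "We will used intention-to-treat analysis to calculate the relative risk, the risk difference, the number needed to treat and the 95% confidence intervals". It mentions no model, covariate or stratum, and it does not exclude them.

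Section 3.6 (Randomization) has the physician answer four questions on the outside of the envelope and only then open it. Answer (a) is the probability of TB. Answer (c) is "in his/her opinion, should the patient begin anti-TB treatment (yes or not"). The procedure is said to protect concealment and to allow the success of the randomisation to be checked. No use of the answers in the analysis is described.

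Section 3.1 lists two locations, a university hospital complex and "Policlínica Augusto Amaral Peixoto (PAAP"). Stratification of the envelope list by location is not described.

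Section 3.10 bases the size on this: "the smallest absolute difference considered important by a panel of specialists working at HUCFF was 10" per cent, with an "80% chance of detecting this difference at the 5% level of statistical significance". It adds: "We intended to recruit at least 770 participants".

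**The concern.** If prescribing follows the physician's opinion, a patient marked yes on (c) can change mainly by stopping treatment, and a patient marked no mainly by starting it. These are different events, and there is no particular reason for them to be equally frequent. If their frequencies differ, part of the outcome variance is explained by something known before allocation. A crude comparison leaves that part in the standard error.

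A second, smaller point is that sections 3.6 and 3.11 both compare the arms at baseline without saying what follows if they differ. In an open trial it is better to name the covariates in advance than to decide on adjustment after seeing an imbalance.

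At stake are the width of the primary confidence interval and some power.

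**Working it through.** **Inputs.** From section 3.10: a 10-point difference, 80% power, 5% level, at least 770 patients. Assumed because not stated: two-sided test, 1:1 allocation (385 per arm), no dropout, change rates of 40% v 50%.

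**Step 1: reproduce 770.** With unpooled variance, n per arm = [p1(1−p1) + p2(1−p2)] × (1.960 + 0.842)² / (p2−p1)² = (0.24 + 0.25) × 7.85 / 0.01 ≈ 385, so 770 in total. The same total results at 50% v 60%. The pooled formula gives 776. The stated size therefore fits an unadjusted two-proportion calculation with change rates around 40% to 60%.

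**Step 2: crude precision.** SE = √(0.49/385) = 0.0357. The 95% half-width is 7.0 points. Power = Φ(0.10/0.0357 − 1.96) = 80.0%.

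**Step 3: exact stratified cases.** Take half the patients yes on (c) and a 10-point effect in each stratum. The variance sum is then the average within-stratum variance in each arm, added over arms.

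| Control change rates, no / yes on (c) | Variance sum | Ratio to 0.49 | Power | Equivalent crude N (770/ratio) |
|---|---|---|---|---|
| 20% / 60% | 0.20 + 0.21 = 0.41 | 0.837 | 86.5% | 920 |
| 25% / 55% | 0.2175 + 0.2275 = 0.445 | 0.908 | 83.7% | 848 |
| 30% / 50% | 0.23 + 0.24 = 0.47 | 0.959 | 81.7% | 803 |

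**Step 4: vary the split.** With share s answering yes, gap g in change rates and 45% changing overall, R² = s(1−s)g² / (0.45 × 0.55), and the adjusted variance is the crude variance × (1−R²). For s = 0.3 and g = 0.4, R² = 0.0336/0.2475 = 0.136.

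| Gap in change rates | Power, 20% yes | Power, 30% yes | Power, 50% yes |
|---|---|---|---|
| 10 points | 80.3% | 80.4% | 80.4% |
| 20 points | 81.1% | 81.4% | 81.6% |
| 30 points | 82.3% | 83.1% | 83.6% |
| 40 points | 84.1% | 85.4% | 86.5% |

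For a given gap, an even split favours adjustment most.

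**Step 5: simulation.** There were 4000 runs per setting, with 30% yes and a linear model with arm-by-covariate interaction and robust variance. Crude and adjusted estimates both averaged about 0.10.

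| Gap | Empirical SE, crude v adjusted | Power, crude v adjusted |
|---|---|---|
| 0 | 0.0356 v 0.0356 | 80.8% v 80.9% |
| 20 points | 0.0356 v 0.0348 | 81.0% v 82.7% |
| 40 points | 0.0360 v 0.0335 | 80.2% v 84.5% |

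When the covariate is uninformative, adjustment costs nothing visible.

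**The case against.** The strongest reply is that there is no error here. Section 3.11 is silent on adjustment and does not forbid it. Covariates are often named in a statistical analysis plan, and that plan is not to hand. This stands as a limit on the point: it proposes a better method and does not correct a mistake. It does not remove the point, because section 3.11 does list the estimators, and as written they describe a plain two-group comparison.

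Several stronger readings are tempting, and the protocol does not support them:

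- **That the crude estimate is biased or unsafe.** It is not. With half answering yes, the chance difference in the yes share has SD √(2 × 0.25/385) = 3.6 points. A 1.96-SD imbalance (7.1 points) with a 40-point gap would move the estimate by about 2.8 points, but the crude 95% interval already allows for this.
- **That adjustment is needed to reach 80% power.** Step 1 shows that it is not. The lack of spare power also depends on the assumed base rate: at 10% v 20%, 385 per arm gives about 97%.
- **That answer (c) must be among the strongest predictors.** It bears on the direction of a possible change, not necessarily on its probability. If both groups change equally often, it predicts nothing.
- **That site is recorded for every patient.** It is known by design from the two named locations, but section 3.6 does not list it among the data collected.
- **That a gain of 6 to 7 power points, or 150 patients, should be expected.** That needs a 40-point gap and an even split.

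The statement in section 3.11 that no subgroup analysis is pre-specified is no obstacle, since adjustment still estimates one overall effect.

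**Conclusion.** The point holds as a matter of efficiency and pre-specification. The planned comparison is valid and consistent with the sample size, but it leaves unused two baseline answers obtained before allocation is known.

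Under the assumptions listed, with gaps of 0 to 40 points by answer (c), power rises by about 0 to 7 points. At the upper end the interval half-width falls from 7.0 to 6.4 points (1.96 × √(0.41/385)). A 50-point gap would give more: 88.5% power with 30% yes and 90.0% with an even split. The protocol gives no change rate by answer (c) and no split, so the place within this range is unknown. The gain may be negligible, and the simulation shows no loss when it is.

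**What to change.** Pre-specify as the primary analysis the marginal risk difference and relative risk with 95% confidence intervals, standardised over all randomised patients from a regression on arm, answer (c), answer (a) and enrolling site. Include an arm-by-(c) term, because starting and stopping are different events and a common effect should not be imposed. For the same reason a Mantel-Haenszel relative risk pooled over the (c) strata suits poorly. Derive the number needed to treat from the standardised risk difference, and report the crude estimates as supporting analysis.

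State that site will be entered in the database. Link answer (c) to the prescription actually made, since an opinion may differ from it. Use answer (c) itself as the covariate: it is fixed before the envelope is opened, whereas the protocol does not say when the initial prescription is recorded.

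The cost is a few sentences, somewhat more analysis work and that data link. It needs no extra patients and no new clinical question.
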